##### Adherence rate

The adherence rate is the proportion of participants who attended 80% of the DSM coaching (group + individual) sessions. Adherence rate will be calculated as Adherence rate = (NA/NP) × 100, where NA is the number of participants who attended 80% of the sessions, and NP is the total number of participants.

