#### Sample size determination

A formal sample size calculation will not be applied for a feasibility RCT study [34]. Hertzog [35] suggests that a sample size of 10–40 participants per group is enough for feasibility studies (Hertzog, [35]. Hence, considering the study’s pilot nature, the intervention’s high intensity, and the limited research fund, we will recruit 40 participants. Twenty participants will be allocated to each arm of the study with a 1:1 ratio.

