**Fig 1 Fig1:**
[figure not shown]
Study participant flow diagram based on the CONSORT guideline [29]. Key: *T1*, *T2*, *T3* represent time of assessment, *n* number

*Treatment group:* The treatment group will attend a 12-week DSM coaching program culturally adapted from the I-change model [27], an evidence-based health coaching intervention [20]. The DSM coaching program will have six interactive group sessions, including an overview of diabetes, goal setting, dietary management, exercise, blood glucose monitoring and medication, and foot care. In addition, the DSM coaching will also include four individual home-based coaching sessions. Furthermore, a family member who is a direct care provider will have a 10-min orientation after every individual home-based coaching session with the participants.

The principal investigator, who has completed a coaching and counseling course at Queen’s University, Kingston, Canada, will facilitate the DSM coaching sessions. The coach will deliver six 2-h group coaching sessions every 2 weeks for 3 months. The coach will use interactive discussions, experience sharing, demonstration, and home-take assignments to address the program goals. The intervention group will also continue receiving the usual care in the clinic (see Additional file 1: the DSM coaching program).

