### Outcome measures

#### Primary outcomes

##### Feasibility outcomes

The current study will address the eligibility rate, recruitment rate, retention rates, adherence rate, and the acceptability of the DSM coaching program. The progression criteria will determine the success of the DSM coaching program (Table 1).

**Table 1 Tab1:** Progression criteria for the feasibility of the DSM coaching program

**Feasibility outcomes**	**Operational definitions**	**Progression criteria/success**	**Source of data**
Eligibility rate	It is the proportion of people who fulfill the screening criteria.	$$\ge$$ 50% will be acceptable for the future trial	Screening records
Recruitment capacity (rate)	It is the proportion of eligible individuals willing to give consent and randomized to the study in 2-month period.	$$\ge$$ 80% (32+) recruitment rate.	Record review
Intervention adherence	An intervention adherence is the participant’s compliance with attending all group sessions, and all home-based coaching sessions.	$$\ge$$ 80% adherence rate	Session attendances of individual and group sessions.
Retention	The ability of the program to retain participants in the study. The proportion of study participants who completed the study and evaluated at the end of the intervention T2 and end of follow-up T3.	$$\ge$$ 80% retention rate	Record review
Acceptability	It is the perception of study participants that a given intervention is agreeable, palatable, or satisfactory.	$$\ge$$ 75% TAAS score	TAAS survey
Coaching session fidelity	It is the proportion of individual coaching sessions rated as moderate or high.	$$\ge$$ 80% will be an acceptable level of fidelity.	Coaching sessions fidelity checklist rated by an OT
DSM coaching Program fidelity	The proportion of fidelity assessment for the DSM coaching program	$$\ge$$ 80% will be an acceptable level of fidelity.	DSM coaching program fidelity assessment checklist

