##### Retention rate

The retention rate is the proportion of participants who complete the intervention. The retention rates can be computed as Retention rate = (NA/NR) × 100, where NA is the number of participants assessed at T3, and NR is the number of randomized participants.

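### Adherence means all 10 sessions in Table 1 but 80% of sessions in the text, and its denominator is not limited to the coached arm, so the 80% progression criterion has no single meaning

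*Protocol article*

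**What the plan says.** The Feasibility outcomes section lists adherence among the primary outcomes and says that the progression criteria in Table 1 decide whether the program succeeds. The adherence criterion is a rate of at least 80%.

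- **Adherence, Table 1:** the participant's "compliance with attending all group sessions, and all home-based coaching sessions".
- **Adherence, Adherence rate section:** the share of participants attending 80% of group and individual sessions combined, where "NA is the number of participants who attended 80% of the sessions, and NP is the total number of participants".
- **Sessions:** the treatment group description under Intervention arms states "The DSM coaching program will have six interactive group sessions", plus four individual home-based sessions. The control group continues usual care.
- **Numbers:** under Sample size determination, "we will recruit 40 participants" and "Twenty participants will be allocated to each arm of the study with a 1:1 ratio".
- **Retention, Retention rate section:** in words, "The retention rate is the proportion of participants who complete the intervention". In the formula, "NA is the number of participants assessed at T3", divided by the number randomised.
- **Retention, Table 1:** those who "completed the study and evaluated at the end of the intervention T2 and end of follow-up T3", with a criterion of at least 80%.

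**The concern.** Two attendance rules feed one threshold, and nothing in the article says which governs. The denominator is also left open, although half the trial is offered no sessions. The same attendance sheets could therefore support either verdict on a primary feasibility outcome that informs the decision on a definitive trial. The definition could be settled after attendance is known. This matters more here because the principal investigator both delivers the coaching and analyses the data.

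Retention has a milder form of the problem. The prose refers to completing the intervention, which control participants never receive. Table 1 mentions T2 as well as T3, while the formula uses T3 alone.

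**Working it through.** The 80% threshold is a chosen cut-off, so there is no derived figure to reproduce. The check is what each wording implies.

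**Inputs from the protocol article.** 40 participants, 20 per arm; 6 + 4 = 10 sessions; 80% of 10 = 8 sessions; criterion at least 80%.

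**Assumptions not in the document.** Attendance probability per session p, taken from 0.80 to 0.98. Sessions are either independent within a person or correlated at 0.3.

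**Step 1: denominator.**
- Literal reading, 40: 0.80 × 40 = 32 adherent participants are needed, but only 20 can attend. The maximum rate is 20/40 = 50%, so the criterion fails even with perfect attendance.
- Coached arm, 20: 0.80 × 20 = 16 are needed.

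**Step 2: probability q that one participant counts as adherent, sessions independent.**
- All 10: q = p^10. At p = 0.90, q = 0.349.
- At least 8 of 10: q = P(Bin(10, p) ≥ 8). At p = 0.90, q = 0.930.

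For the expected rate to equal 80%, the all-10 rule needs p = 0.80^(1/10) = 0.978. The 8-of-10 rule needs p = 0.842.

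**Step 3: probability that the criterion is met, P(Bin(20, q) ≥ 16).**

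| p (assumed) | q, all 10 | q, at least 8 | P(met), all 10 | P(met), at least 8 |
|---|---|---|---|---|
| 0.80 | 0.107 | 0.678 | 0.00 | 0.18 |
| 0.85 | 0.197 | 0.820 | 0.00 | 0.72 |
| 0.90 | 0.349 | 0.930 | 0.00 | 0.99 |
| 0.95 | 0.599 | 0.988 | 0.05 | 1.00 |
| 0.98 | 0.817 | 0.999 | 0.70 | 1.00 |

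**Step 4: clustering of attendance within people.** Use a beta-binomial with mean p and correlation ρ = 0.3, so that α = p(1/ρ − 1) and β = (1 − p)(1/ρ − 1). At p = 0.90, α = 2.10 and β = 0.233.
- p = 0.90: 64% attend all 10 and 85% at least 8; P(met) is 0.10 against 0.83.
- p = 0.95: 80% and 93%; P(met) is 0.64 against 0.99.

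**Step 5: retention.** The criterion needs 32 of 40. Suppose, for illustration, that 10% (4) are missed at T2 and 15% (6) at T3.
- T3 formula: 34/40 = 85%, which passes.
- T2 and T3 both required: between 30/40 = 75% (no overlap) and 34/40 = 85% (all four also missed at T3). With independent misses, 0.90 × 0.85 = 76.5%.

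The two versions differ only for people seen at T3 but missed at T2.

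**The case against.** The strongest reply is that the intended meaning can be inferred. The adherence numerator counts attendance at coaching sessions, the data source is the attendance sheets, and only the treatment group has sessions. The symbol NP also differs from NR, which the recruitment and retention formulas use for those randomised. On that view the denominator is plainly the coached arm. This largely stands: a reader might infer that the trial has set itself an impossible criterion, but the article never says that the denominator is 40. The 50% ceiling shows that a qualifier is missing, not that anyone would apply the rule that way.

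It can also be said that Table 1 merely names which sessions count, while the Adherence rate section holds the only formula. That is a possible reading, but Table 1 labels its entry an operational definition and places it beside the threshold, and nothing tells the reader to prefer the formula.

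Independence between sessions is a poor model, since attendance tends to cluster within people, and reminder calls and agreed schedules may raise it. This narrows the gap, as Step 4 shows, but does not remove it at 90% or 95%.

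On retention, a reader might infer three conflicting definitions. The article does not support that: the formula is explicit, and Table 1 may simply mean reporting at each time point, as Table 2's several ticks for retention suggest. A reader might also want 80% retention required in each arm, because a pooled 32/40 could combine 20/20 controls with 12/20 coached. Pooled retention is a legitimate feasibility measure, however. A by-arm threshold would be a new, stricter criterion, not the repair of a contradiction.

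**Conclusion.** The concern holds for adherence. Two incompatible attendance rules serve one progression criterion, and the denominator is not restricted to those offered sessions. This follows from the text and needs no assumption.

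Its size does depend on assumptions. With 20 as denominator and 90% attendance per session, the chance of meeting the criterion is 0.99 against 0.00 under independence, or 0.83 against 0.10 with a within-person correlation of 0.3. The gap narrows at higher attendance: at 98% with independence it is 1.00 against 0.70, and at 95% with correlation it is 0.99 against 0.64. The 8-of-10 rule is not lenient in itself; at 80% independent attendance it is met with probability only 0.18.

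The claim that the criterion is unattainable rests on the literal denominator of 40 and should not be put more strongly than that. Retention is a secondary wording matter.

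**What to change.** **Adherence.** Use one definition in Table 1 and in the Adherence rate section: participants randomised to coaching who attended at least 8 of the 10 sessions, divided by all participants randomised to coaching (n = 20). State that the criterion is met at 16 of 20. Remove the requirement of all group and all home-based sessions from Table 1.

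**Retention.** Keep the existing formula, assessed at T3 divided by randomised. Delete the phrase about completing the intervention. Make Table 1 say whether T2 is reported separately or is also required for the criterion. Report retention by arm descriptively, without a by-arm threshold.

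**Cost.** Edits to two rows of Table 1 and two short sections. The attendance and assessment records needed are already planned, and sample size, randomisation and data collection do not change. The wording should be fixed before attendance data are examined.

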##### Acceptability

Acceptability determines how well the target population receives a program and how it meets the needs of the target population [39]. Acceptability of the DSM coaching program will be assessed using the Treatment Acceptability/Adherence Scale (TAAS) [40]. The TAAS is a 10-item Likert scale with a value ranging between 1 and 7.

##### Fidelity of the DSM coaching program

The fidelity of the DSM coaching program will be assessed using the Comprehensive Intervention Fidelity Guide (CIFG) designed by Gearing. The CIFG is a guide with four core elements: design, training, delivery, and receipt fidelity proposed to examine an overall intervention fidelity [41]. The DSM Coaching Fidelity Measure (DSMC-FM) will assess the fidelity of the DSM coaching sessions. The DSMC-FM is informed by the Occupational Performance Coaching-Fidelity Measure (OPC-FM) [42]. The DSMC-FM has 23 items, of which 16 are critical components that focus on the coach’s behavior and practices. Four items address the client’s responses and behavior,the rest (3 are distinguished items needing improvement. An occupational therapist will review the recordings of the DSM coaching individual sessions and assess the fidelity of the coaching sessions.

### Secondary outcomes

The secondary outcomes of the study encompass self-efficacy, self-care activity, quality of life, and HbA1c. These outcomes will be assessed at baseline (T1), post-intervention (T2), and post-follow-up period (T3) (Table 2).A. Self-care activityThe diabetes self-care activity is the ability of an individual with type 2 diabetes to follow a healthy eating plan, perform regular exercise, monitor blood glucose, perform foot care, adhere to diabetes medication/s, and cease cigarette smoking [43]. Self-care activity will be measured using the Summary of Diabetes Self-Care Activity tool (SDSCA) [43]. The tool will be culturally translated and validated for face and content validity by a panel of experts.B. Self-efficacySelf-efficacy is an individual’s belief and confidence in their ability to perform intended activities that affect their life and control over how these activities are experienced [44, 45]. Self-efficacy will be measured using the Stanford Self-Management Resource Center (SMRC) diabetes self-efficacy scale, which has an eight-item Likert Scale [46]. The tool will be translated into the local language, Amharic, and undergo content validation by a panel of experts.C. Quality of lifeAs defined by the WHO, quality of life is an individual’s perception of their position in life in the context of the culture and value systems in which they live and their goals, expectations, standards, and concerns [47]. The quality of life of individuals with type 2 diabetes will be assessed by a valid and reliable WHOQOL-BREF tool [48]. The tool has demonstrated reliability and construct validity [48]. The WHOQOL-BREF tool has 26 items addressing the physical, psychological, social, and environmental health domains with five ordinal scales [48].D. Glycated hemoglobin A1CHbA1C is a reliable measure of long-term glucose monitoring recommended by the WHO and the American Diabetes Association (ADA) [49]. HbA1c < 7% is considered good glycemic control, and HbA1c equal to or greater than 7% will be regarded as an uncontrolled glucose level [50].

**Table 2 Tab2:** Outcome assessment timeline showing list of assessment items (outcomes) and corresponding evaluation time

**Outcome variables**	**Assessment time in weeks**												
	T1–W0	W1–3	W4	W5	W6	W7	W8	W9	W10	W11	W12	T2–W13	T3–W24
**Acceptability**													﻿√
Eligibility rate	√												
**Recruitment**	√												
Retention rate	√										√		√
**Adherence rate**		√	√	√	√	√	√	√	√	√	√		
TAAS												√	
**Fidelity-CIFG**	√	√	√		√		√		√		√		
DSMC-FM				√		√		√		√			
**Self-efficacy**	√											√	√
Self-care practice	√											√	√
**Quality of life**	√											√	√
HbA1c	√											√	√
**Blood pressure**	√											√	√
Body mass index	√											√	√

*T1* baseline, *T2* post-intervention assessment, *T3* post-follow-up assessment, *W* week

#### Data collection

Data on participants’ demographic, behavioral, and clinical characteristics will be collected through interviews and reviewing patient medical records. Clinical characteristics such as HbA1c and blood pressure will be retrieved using a chart review form. The weight and height of participants will be measured during their clinical visit to compute body mass index.

Data on self-care activities, self-efficacy, and quality-of-life will be collected using an interviewer-administered data collection technique at baseline (T1), at the end of the intervention (T2), and at the end of the follow-up period (T3). All three data collection periods will be scheduled at least 2 weeks after the holidays as the dietary practice during holidays affects study outcomes. Three MSc nurse data collectors will receive a 1-day training on questionnaire administration procedures, the study instruments, study blinding, and ethical issues related to data collection. Each data collector will work only once to keep the data collectors masked about group allocation. Additionally, all study participants will attend a 5-min orientation to ensure they do not disclose their group to the data collector during the interview. Data related to the quantitative feasibility outcomes: eligibility, recruitment, adherence, and retention rate, will be collected from the recruitment documents, session attendance sheets, and assessment reports throughout the study process. The TAAS assessment will be carried out along with post-follow-up data collection. However, only the treatment group participants will be asked about the program’s acceptability.

### Study participant retention

Retaining adequate study participants is challenging for many interventional studies involving human subjects. Studies suggest different strategies to increase the retention rate [51, 52]. One of the strategies to retain participants in this study is building effective relationships and treating participants respectfully and compassionately. Hence, the research assistants and data collectors will demonstrate respect and compassion for the study participants. A close follow-up throughout the study period will be the other mechanism to ensure participant retention. The research assistant will closely follow participants through regular attendance and make reminder calls before each session. The research assistant, principal investigator, and participants will discuss and arrange meeting schedules for the group coaching and individual home-based coaching sessions. Participant transport costs will be covered to encourage their participation. In addition, with tangible evidence, any cost incurred by the participant for the purpose of the study will be refunded. The group session will be designed to create active participation through discussion, role play, and demonstration, which will make the sessions attractive and enhance participation.

### Data analysis and management

An independent statistician will enter, code, and clean the data using Epi-Info version 7.3.2. The data will be imported to SPSS version 29 for analysis**.** The principal investigator will analyze the data in consultation with statisticians and the research team. An intention-to-treat (ITT) analysis technique will be followed to analyze the quantitative data [53]. An ITT analysis will run data of all participants irrespective of their adherence to the program [54], and missing values will be filled using multiple imputation techniques [55]. Baseline differences between the treatment and control groups will be examined using *t*-tests. Frequencies, percentages, mean, median, standard deviation, and interquartile range will be computed to describe the population. A *p*-value < 0.05% with a 95% confidence level will be used to determine statistical significance.

Differences in the effect size of the secondary outcomes of the study will be computed following a test of assumptions. For normally distributed continuous outcomes, the mean difference within and between the groups will be determined by paired sample Student *t*-test and independent sample Student *t*-test, respectively. Non-parametric tests such as the Mann–Whitney *U* test, Wilcoxon signed rank test, and Friedman analysis of variance test will be computed to determine the median difference for variables that violate the normality assumption. A repeated measure analysis of variance will be considered to estimate the variance between the baseline, post-intervention, and post-follow-up measurements. If a difference is detected between the two groups, a covariate analysis approach or multivariate analysis technique will be considered to rule out the effect of covariates using the pretest score and age of the participant as the covariate.

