**Methods:**

The study will employ a mixed-method feasibility randomized controlled trial design. Forty individuals with type 2 diabetes will be randomly allocated to treatment and control groups using block randomization. The primary feasibility outcomes include acceptability, eligibility, recruitment, and participant retention rates, which will be computed using descriptive analysis. The secondary outcomes are self-efficacy, self-care activity, quality of life, and glycated hemoglobin A1c. For normally distributed continuous variables, the mean difference within and between the groups will be determined by paired sample Student *t*-test and independent sample Student *t*-test, respectively. Non-parametric tests such as the Mann-Whitney *U* test, the Wilcoxon signed rank test, and the Friedman analysis of variance test will determine the median difference for variables that violated the normality assumption. A repeated measure analysis of variance will be considered to estimate the variance between the baseline, post-intervention, and post-follow-up measurements. A sample of 10 volunteers in the treatment group will participate in the qualitative interview to explore their experience with the diabetes self-management coaching program and overall feasibility. The study will follow a qualitative content analysis approach to analyze the qualitative data. Qualitative and quantitative findings will be integrated using a joint display technique.

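### The stated significance threshold, p < 0.05% (0.0005), conflicts by a factor of 100 with the 95% confidence level in the same sentence, very probably through a stray percent sign

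*Protocol article*

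**What the plan says.** The rule stands in the protocol article under *Data analysis and management*. Its sentence on p-values reads "value < 0.05% with a 95% confidence level will be used to determine statistical significance". No other significance level appears in the article. The Methods part of the abstract lists the tests without one, and there is no multiplicity adjustment or other reason for an unusually strict threshold.

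The same section names the tests that the rule would govern. For normally distributed outcomes, "the mean difference within and between the groups will be determined by paired sample Student" t-tests and independent-sample t-tests respectively. Rank-based tests are planned where normality fails, and a repeated-measures analysis of variance across the three assessments. A covariate analysis, using the pretest score and age, is to be considered only if the two groups are found to differ.

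Two other statements limit the reach of the rule:

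- The abstract says of the primary feasibility outcomes that they are rates "which will be computed using descriptive analysis".
- *Sample size determination* says "A formal sample size calculation will not be applied for a feasibility RCT study" and "Twenty participants will be allocated to each arm of the study with a 1:1 ratio".

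**The concern.** A significance threshold and a confidence level are two expressions of one quantity: the threshold is one minus the confidence level. Here they are given together and do not match. Anyone applying the sentence has to choose which half to follow.

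The choice affects how the secondary outcomes are reported. For the same t-test, a 95% interval excludes zero exactly when p < 0.05. If significance is instead declared at 0.0005, some results will have an interval that excludes zero and a verdict of not significant. The choice also affects the covariate analysis, because no other rule says when a difference between the groups counts as found.

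This is not a detail left for a fuller protocol or an analysis plan. The article states the rule and states it inconsistently.

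**Working it through.** **Inputs from the protocol article**

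- Threshold as written: 0.05% (*Data analysis and management*).
- Confidence level: 95% (same sentence).
- Between-group test for normally distributed outcomes: independent-sample t-test (same section).
- Sample size: 40 in total, 20 per arm (*Sample size determination*).

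**Assumptions, because the article gives no figure**

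- Two-sided testing.
- True standardized differences of 0.5, 0.8 and 1.0 SD, taken as a range.

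**Step 1. Do the two halves of the sentence agree?**

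- Threshold as written: 0.05 / 100 = 0.0005.
- Threshold implied by the confidence level: 1 − 0.95 = 0.05.
- Ratio: 0.05 / 0.0005 = 100.

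The stated threshold cannot be reproduced from the stated confidence level. One-sided testing does not help, since 95% confidence then corresponds to 0.05 or 0.025, never 0.0005. If 0.0005 were intended, the matching level would be 1 − 0.0005 = 99.95%. Without the percent sign the two halves agree exactly.

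**Step 2. Which results would be classified differently?**

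Degrees of freedom are 20 + 20 − 2 = 38. The smallest observed standardized difference that reaches significance is t_crit × √(2/20) = t_crit × 0.316.

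- At 0.0005: t_crit = 3.81, giving 1.20 SD.
- At 0.05: t_crit = 2.02, giving 0.64 SD.

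Observed differences from 0.64 to 1.20 SD have 0.0005 ≤ p < 0.05. Their 95% interval excludes zero, but they fail the literal rule. Outside that band the two readings give the same answer.

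**Step 3. What would the literal rule do to power?**

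Power = 1 − F(t_crit) + F(−t_crit), where F is the noncentral t distribution function with 38 degrees of freedom and noncentrality d × √(20/2) = 3.162 d.

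| Assumed true difference | Power at 0.0005 | Power at 0.05 |
|---|---|---|
| 0.5 SD | 2% | 34% |
| 0.8 SD | 13% | 69% |
| 1.0 SD | 29% | 87% |

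The true difference detectable with 80% power is 1.49 SD at 0.0005 and 0.91 SD at 0.05.

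These figures cover the between-arm t-test only. Power for the paired, Wilcoxon, Friedman and repeated-measures analyses also depends on the within-person correlation, which the article does not give, so it was not calculated.

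**The case against.** The strongest defence is that nobody would apply the literal rule. The 95% level in the same sentence shows what was meant, nothing in the article argues for 0.0005, and the analysis is to be done in consultation with statisticians. On that view the power figures describe something that will not happen. Most of this stands, and it is why the point is minor. It does not make the sentence correct: a prespecified rule should have one reading, and this one has two.

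A reader might also infer more than the article supports:

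- **That the feasibility verdict is at risk.** It is not. Table 1 sets seven progression criteria as percentages, and these decide the success of the program. None uses a p-value, and the primary outcomes are descriptive. The faulty figure is the only p-value threshold, not the only quantitative threshold.
- **That the sample size is wrong.** The 40 participants were not derived from any significance level, and the article says so openly. Limited power at 0.05 is a known feature of the design and a separate matter from this contradiction.
- **That tests and intervals would disagree throughout, or that nearly every result would be negative.** They disagree only for 0.0005 ≤ p < 0.05. How often that happens depends on the true effect, which is unknown, and it was worked out only for the between-arm t-test.
- **That p-values should be barred from supporting any statement about effectiveness.** That is a preference about reporting pilot trials. Curing the contradiction does not require it.

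**Conclusion.** The sentence is wrong as written: its threshold and its confidence level differ by a factor of 100. The cause is very probably a stray percent sign. The effect is confined to the inferential analyses of self-efficacy, self-care, quality of life and HbA1c, and to the covariate analysis conditional on a group difference.

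If the rule were followed literally, the consequence for those analyses would be material: the observed difference needed for significance would nearly double, and power at a moderate to large effect would fall sharply. These sizes rest on two-sided testing, 20 analysed per arm, the independent t-test and the assumed range of effects.

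Severity is minor, because the intended value is clear and the primary objective is unaffected. Confidence in the contradiction itself is high, since it needs no assumption.

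**What to change.** In *Data analysis and management*, replace the threshold with: two-sided p < 0.05, with 95% confidence intervals. Removing the percent sign cures the contradiction. Adding *two-sided* also states the sidedness, which the article leaves open and the sponsor should confirm. If 0.0005 was in fact intended, the sponsor should say why and change the confidence level to 99.95%.

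The cost is one sentence. Design, sample size, data collection and progression criteria stay as they are.
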